### Intervention Group and Control Group Activities

**The control group **will continue with "usual care" for the subsequent six months without interruption, including all activities and service use recommended by treating health professionals. In addition, participants in the control group will receive a home programme involving six home visits for the six month period by an Occupational Therapist, to provide an information/education and support programme. Topics to be covered in the programme include issues around diagnosis; community services; occupational performance (including issues around grief and losses); and environmental safety and aids. The programme will avoid any messages encouraging any change in activities that may influence balance and mobility performance. Control participants will receive phone calls from the Occupational Therapist to follow up on issues raised in the home visits between home visits.

**The intervention group **will participate in a tailored (individualised) home based balance exercise programme, provided by a physiotherapist. This exercise programme is based on an existing home exercise programme (the Otago programme, ), which has been shown to improve balance and reduce falls in older people without cognitive impairment in the community setting [50-52]. The programme has been modified to provide increased support and visits in the early stages of exercising. Appropriate exercises from the Otago programme will be selected by the physiotherapist, and be tailored to balance and mobility problems identified from the assessments. Participants will receive six home visits during the six month duration (two visits in the first month after the baseline assessment, two further visits in the second month, then two more home visits four to six weeks apart for the remaining times). An exercise booklet will be provided by the physiotherapist to each participant or carer to give illustrations and instructions for the participant to continue the exercise programme at least five times a week. In between visits, the physiotherapist will contact participants by telephone (five phone calls during the six month duration). Adherence to the programme will be monitored by daily completion of an exercise diary. All participants will also continue to receive 'usual care'.

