### Primary Outcome Measures

Two primary outcome measures have been selected: Limits of Stability (LOS) test (Maximum Excursion measure) (Neurocom Balance Master™) and the Step Test. All other measures will be considered as secondary outcomes. The LOS Maximum Excursion measure is a dynamic balance measure which has been shown to be a sensitive measure of balance impairment, and to be responsive to exercise interventions in older populations [38,40,53]. The Step Test is a simple clinical balance measure which is routinely used in clinical practice and research in the field of balance and falls prevention. It has high reliability [42] and is sensitive to change in balance performance in older people with clinical conditions such as Parkinson's disease [54,55] and stroke patients [42,56], and is responsive to change following an exercise intervention [57].

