### Statistical Analysis

Intention to treat analysis will be used. Balance performance on the two primary outcome measures and the secondary outcome measures will be made using repeated measures ANOVA between the two groups, with variables differing between groups at baseline being used as covariates. Multivariate logistic regression will be used to evaluate factors associated with improved outcomes, including level of adherence to the exercise programme. For the longitudinal sub-study, independent sample *t*-tests will be used to determine differences in balance performance between both groups at each time point.

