### Sample Size

Power analysis was based on data from a recent study of community dwelling older people with mild balance impairment (approximately 15–25% impairment compared to healthy controls), which is in the approximate range of impairment anticipated in our sample with mild-moderate severity Alzheimer's disease. Using data from one of the main force platform measures of balance (Limits of Stability, Maximum Excursion, mean score 71.9; SD 14.3) and a clinical balance measure (Step Test, mean score 14, SD 3.6), power calculations were performed to determine the required sample size to demonstrate a 10% improvement, at 80% power and alpha = 0.05. Using these two tests as primary outcome measures for evaluating the effectiveness of the balance retraining exercise programme, a sample size of 80 per group will be required (160 overall). Assuming a loss to follow up of 25%, a sample of 214 will be required for the main study (RCT study). For the longitudinal sub-study, based on the estimated magnitude of balance impairment (15–25%) relative to healthy age matched controls from previous studies, a sample size of 42 will be sufficient to demonstrate group differences (healthy vs Alzheimer's disease group) on the Limits of Stability Maximum Excursion outcome. Allowing for 20% dropout in this group/year over the 2 year follow-up period for this group, 64 healthy age and gender matched controls (matched to the first 64 participants in the control group) will be required for the longitudinal follow-up component of the study. This sample size will be sufficient to identify significant decline in performance over a two year follow-up period (power 0.8, alpha 0.05, single sided analysis, assuming 7% decline in balance performance/year in the Alzheimer's disease group). Previous studies have shown a change of 1–2% per year on balance and mobility measures for healthy older people [58], and over 10% decline in Activities of Daily Living (including locomotion) in six months in people with moderate severity dementia [59].

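### Logistic regression for improved outcomes forces the numeric balance scores into categories and loses information; adherence, defined only in the exercise arm, should be modelled there on the continuous score

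*Protocol article*

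**What the plan says.** The protocol article, under Primary Outcome Measures, states: "Two primary outcome measures have been selected: Limits of Stability (LOS) test (Maximum Excursion measure) (Neurocom Balance Master™) and the Step Test". Both are numeric: the first is a force-platform score, and the second is a count of steps in 15 seconds, taken on the worse side. In the Statistical Analysis section the group comparison on the primary and secondary measures "will be made using repeated measures ANOVA between the two groups", so there the scores stay on their own scale.

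The next sentence of that section changes method: "Multivariate logistic regression will be used to evaluate factors associated with improved outcomes, including level of adherence to the exercise programme". It names no outcome, cut-point, analysis population or covariate list.

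Adherence appears under Intervention Group and Control Group Activities, in the paragraph on the exercise group only: "Adherence to the programme will be monitored by daily completion of an exercise diary". Controls receive an education and support programme from an occupational therapist, of which the article says: "The programme will avoid any messages encouraging any change in activities that may influence balance and mobility performance". Adherence to the exercise programme therefore has no natural value for a control participant.

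**The concern.** There are two problems, of different standing.

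The first follows from the named method. Logistic regression needs a categorical response. A numeric score can enter it only after being cut, and a cut treats a participant just over the line as equal to one far over it. An analysis plan can supply the cut-point, but no cut-point restores the lost information. The preceding sentence of the same section analyses these scores uncut, so nothing in the design requires the coarser form.

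The second is conditional. If both arms entered one model, controls were coded as zero adherence and allocation was not a covariate, adherence would act as a proxy for allocation. A treatment effect could then be read as a dose-response relation.

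At stake is the only quantitative analysis in the article of who benefits and whether adherence relates to benefit. The Discussion looks ahead to routine provision of such a programme, and an adherence relation that is missed or spurious would bear on that.

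**Working it through.** **Inputs from the Sample Size section.** "Limits of Stability, Maximum Excursion, mean score 71.9; SD 14.3"; "Step Test, mean score 14, SD 3.6"; the aim is "to demonstrate a 10% improvement, at 80% power and alpha = 0.05", with 80 evaluable per group. The recruited total reproduces: 160 / 0.75 = 213.3, rounded up to 214, or 107 per arm if allocation is 1:1. The article claims no power for the logistic analysis, so there is no stated figure of that kind to reproduce. The 80 is used here only as the number of exercise-arm completers.

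**Assumed inputs (not in the article).** The proportion classed as improved; the strength of the adherence association; a baseline to follow-up correlation of 0.7; and, for the pooling check, the distribution of adherence.

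**Step 1: information lost by cutting a normal score.** If a proportion p is classed as improved and c is the matching normal cut, the relative efficiency is ARE = φ(c)² / [p(1 − p)].
- p = 0.5: 0.3989² / 0.25 = 0.637. The loss is 36%, and 80 completers carry the information of about 51.
- p = 0.3: 0.3477² / 0.21 = 0.576. The loss is 42%, and 80 act like about 46.
- p = 0.2: ARE 0.490, a loss of 51%.

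The median split is the most favourable cut.

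**Step 2: what that does to power.** Power = Φ((1.960 + z) × √ARE − 1.960), where z is the normal quantile of the starting power. From 80% (z = 0.842):
- p = 0.5: Φ(2.802 × 0.798 − 1.960) = Φ(0.275) = 60.8%, a relative loss of 24%.
- p = 0.3: Φ(2.802 × 0.759 − 1.960) = Φ(0.166) = 56.6%, a relative loss of 29%.

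At the median split, a starting power of 95% falls to 82% (14% relative) and one of 50% falls to 35% (31% relative). The relative loss is therefore not a constant.

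**Step 3: illustration with baseline in both models.** Simulated score: y = 0.7·baseline + √0.51·(0.3·adherence + √0.91·noise), n = 80. Linear regression of y on baseline and adherence is compared with logistic regression of improved (change score above the cut) on the same two terms.

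| Model | Power |
|---|---|
| Linear | about 76% (75–78% over repeated runs) |
| Logistic, median split | about 53% (53–54%) |
| Logistic, 30% improved | about 45% (45–49%) |

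At a partial correlation of 0.4, the linear model has about 96% against 79–81% at the median split, a relative loss of 16–18%. At 0.5 it has nearly 100% against about 95%, a loss of about 5%.

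**Step 4: the pooling scenario.** The planned effects in SD units are 0.10 × 71.9 / 14.3 = 0.503 for Limits of Stability and 0.10 × 14 / 3.6 = 0.389 for the Step Test. Assume 80 per arm, control adherence of 0, exercise-arm adherence of about 0.6 (SD 0.25), and no adherence effect within the arm. Adherence then correlates about 0.87 with allocation.
- Allocation omitted: adherence is falsely significant in 58% of trials (d = 0.503) or 40% (d = 0.389).
- Allocation included: 4–5%, the nominal level.

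**The case against.** The strongest reply is that this is a supplementary analysis described in one sentence of a condensed article. The treatment effect is tested on uncut scores, no power is claimed for the factors analysis, and responder-type logistic regression is common practice. Cut-point, covariates and population are details that an article may leave to a fuller document. All of this stands, and it is why the point has low priority. It does not remove the point, because the method itself is fixed in the text and the loss follows from the method.

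A reader might infer more than the article supports, in four ways.
- **That the analysis loses a third of its power.** No such figure belongs to this plan. The loss depends on the assumed association, the starting power and a cut-point the article does not give.
- **That most of the information is thrown away.** At the splits considered, 36% to 42% is lost, so most is kept. The loss passes half only near 20% improved.
- **That adherence is confounded with allocation.** The article does not say the arms are pooled, that controls are coded zero or that allocation is left out. An exercise-arm model is at least as natural a reading, and adding allocation removes the artefact.
- **That a low baseline will look like benefit through regression to the mean.** This would require baseline to be left out, and nothing says it is. In a check with no adherence effect and adherence correlated −0.3 with baseline, false positives were 4.5% with baseline in the model and 9.9% without.

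The response could also be an outcome other than the balance scores, such as falls. The point is therefore confined to the numeric balance measures.

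**Conclusion.** The point holds in a limited form. For Limits of Stability and the Step Test, the named method implies categorisation, which costs about 36% of the information at best and about 42% if 30% are classed as improved; these figures assume a roughly normal score. The drop in power from about 76% to 53% or 45% is an illustration under the stated assumptions, not a property of the plan. The pooling problem is a risk left open by an unstated population, not an error in the text. Even in the exercise arm alone, adherence is not randomised, so any relation with outcome is observational. This is a cheap improvement of low priority; the primary comparison is not affected.

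**What to change.** In the Statistical Analysis section, for the balance scores:
- Replace the logistic regression with linear regression of the 6-month score on its own baseline value, fitted separately for Limits of Stability and the Step Test.
- Fit adherence in the exercise arm only, as a continuous variable (for example, the proportion of prescribed sessions recorded as completed in the diary), and report it as associational.
- For baseline factors that may modify benefit, use both arms and test factor-by-group interactions in the same linear model.

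The cost is a change of a sentence or so and no new data. The downside is losing a responder odds ratio; the proportions improved in each group can be kept as a descriptive table.

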
The primary aim of the present project is to implement and evaluate the effectiveness of an individually tailored, home based exercise programme in improving balance and mobility performance in people with mild to moderate severity Alzheimer's disease. A sub-study will be run concurrently, with the aim of evaluating difference in rate of change in balance performance between people with Alzheimer's disease compared to healthy age and gender matched older people.

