### Sub-study – Longitudinal Change in Balance Performance

The first 64 participants recruited for the primary study and randomised to the control group will undergo complete assessments as described in the primary study, but also have further complete assessments at 18 months and 24 months following the initial assessment. Sixty four age and gender matched healthy participants will also be assessed on the full balance assessment battery at 0, 6, 12, 18 and 24 months for comparison of the rate of change in balance performance in the sample with mild to moderate severity Alzheimer's disease.

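### The sub-study aims to compare rates of balance change, but its planned t-tests compare levels at each visit and leave that aim untested

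*Protocol article*

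**What the plan says.** The Background section of the Protocol article gives the sub-study's aim as "evaluating difference in rate of change in balance performance between people with Alzheimer's disease compared to healthy age and gender matched older people". The section on the sub-study repeats it: healthy participants are to be "assessed on the full balance assessment battery at 0, 6, 12, 18 and 24 months", and the purpose is given as "for comparison of the rate of change in balance performance in the sample with mild to moderate severity Alzheimer's disease".

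The Statistical Analysis section assigns repeated measures ANOVA to the trial's primary and secondary outcomes. It then gives the sub-study a sentence of its own with a different method: independent-sample t-tests "will be used to determine differences in balance performance between both groups at each time point". No other sub-study analysis is named.

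The Sample Size section supports the sub-study in two ways. It first gives 42 as enough to show a group difference on Limits of Stability, from an expected impairment of 15–25% relative to healthy controls, and raises this to 64 for 20% dropout per year over two years. It then states that this number can detect decline over two years, on the basis of a "single sided analysis, assuming 7% decline in balance performance/year" in the Alzheimer's group. It also cites a change of 1–2% per year in healthy older people.

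**The concern.** The aim concerns a difference between two rates. The analysis is five separate comparisons of mean level, at 0, 6, 12, 18 and 24 months. None of them contains a change, a slope or a group-by-time term.

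The two groups are expected to differ at the outset, so a significant result at any visit may show only the deficit already present at baseline. A reader who sees significance at 24 months could take it as faster decline in Alzheimer's disease when the test carries no such information. A run of p-values over time does not help either, because it also moves with the number of people remaining and with who they are.

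Some lesser losses follow. The tests ignore the correlation between a person's repeated measurements, which is the main gain from following the same people. They ignore the age and gender matching. They give five tests per measure with none named as the main one. The power statement concerns decline in one group, not the contrast between groups that the aim names.

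**Working it through.** **Inputs from the Sample Size section.** "Limits of Stability, Maximum Excursion, mean score 71.9; SD 14.3"; expected deficit 15–25%; decline 7% per year in Alzheimer's disease and 1–2% per year in healthy people; 64 per group; 20% dropout per year.

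**Assumptions.** Percentages are taken of 71.9, and SD 14.3 applies to both groups. The within-person correlation ρ between visits is not given, so a range is shown.

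**1. The plan's own figures.** 42 / 0.8² = 65.6, against 64 stated. In reverse, 64 × 0.8² = 41 completers per group. The dropout step is therefore reproduced to within two people. The base figure of 42 is less clear. By the usual normal-approximation formula, a 15% difference in level needs 22 per group one-sided (44 in total) or 28 per group two-sided. So 42 comes close only as a one-sided total, although it is inflated as a per-group number. On either reading it is sized for a level, not a rate.

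**2. What the t-tests do when the rates are equal.** With equal decline, the gap at every visit equals the baseline gap.

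- Gap of 15%: 0.15 × 71.9 = 10.8 points; d = 10.785 / 14.3 = 0.754.
- Noncentrality = d × √(n/2): 0.754 × √32 = 4.27 at n = 64, and 0.754 × √20.5 = 3.41 at n = 41.
- Probability of significance (noncentral t, two-sided 0.05): 98.9% at n = 64 and 92.1% at n = 41.
- Gap of 25%: over 99.9% at either size.

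The drop from 99% to 92% comes only from the falling number of participants; nothing about balance has changed.

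**3. Equal against different rates.** Simulation of five visits with 41 per group, equal correlation between all visits, 4,000 runs, two-sided 0.05:

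| Baseline gap | Decline per year, healthy vs Alzheimer's | Visit t-tests significant | Slope comparison significant, ρ = 0.5 / 0.7 |
|---|---|---|---|
| 15% | 1.5% vs 1.5% | 92–93% at each visit | 5% / 5% |
| 15% | 1.5% vs 7% | 92% at baseline, 100% at 24 months | 80% / 95% |
| 25% | 1.5% vs 1.5% | 100% | 6% / 5% |
| 25% | 1.5% vs 7% | 100% | 79% / 94% |

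The t-tests barely separate the two situations. The slope comparison does.

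**4. Power for the contrast that the aim names.**

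- Net difference over two years: (7% − 2%) × 2 = 10%, or 7.2 points, to (7% − 1%) × 2 = 12%, or 8.6 points.
- SD of change = 14.3 × √(2(1 − ρ)): 14.3 at ρ = 0.5 and 11.1 at ρ = 0.7.
- Power with 41 per group, baseline to 24 months, two-sided: 61–77% at ρ = 0.5 and 83–94% at ρ = 0.7.
- On the plan's one-sided basis: 73–86% and 90–97%.

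**The case against.** The strongest reply is about reach. The sub-study is a non-randomised cohort beside the trial. No randomised comparison, primary outcome or main sample size is touched, and the analysis can be corrected before the data are analysed. That stands: the defect is confined to the sub-study, but there it affects the only aim.

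Second, the sample is roughly adequate. The lower power figures above come from a two-sided test and from a change score that uses two of the five visits; a slope test on all five reaches about 80% two-sided at ρ = 0.5. This also stands. The fault lies in the test and in the justification of the sample size more than in the number recruited.

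Third, it would overstate the case to say that all five t-tests are certain to be significant. With a 15% gap, equal rates and numbers falling from 64 to 41, all five are significant together in roughly 84–89% of simulated runs, depending on ρ and on the numbers at the middle visits. At a 20% gap it is about 99%.

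Fourth, the Missing data section plans maximum likelihood and multiple imputation. It is worded for intention-to-treat analyses, so its reach to the sub-study is unclear. If applied, it would ease the dropout problem, but it cannot turn a test of levels into a test of rates.

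Finally, matching and multiplicity are secondary. Independent-sample tests on matched groups are usually a little conservative, not invalid, and multiplicity rules are often left to an analysis plan. The choice of method is different: the article names it, so it is not a detail left open.

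**Conclusion.** The concern holds. As written, the plan tests group differences in level at five visits and never tests the difference in rate of change that it sets as the sub-study's aim. On its own figures, with no difference in rate, each t-test is significant with probability 92–99% at a 15% gap and almost always at 25%.

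This rests on SD 14.3 in both groups and on percentages of 71.9. If 71.9 is instead the impaired group's mean and the deficit is relative to healthy people, the 15% gap becomes 71.9 / 0.85 − 71.9 = 12.7 points, which strengthens the result. The conclusion about the t-tests at a single visit does not depend on ρ. The power figures for change do, and they assume no extra person-to-person variation in slope; such variation would lower them. The correction is necessary for the sub-study and does not affect the randomised comparison.

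**What to change.** Replace the visit-wise t-tests with one linear mixed model on all five visits: group, time and group-by-time as fixed effects, a random intercept and slope per person, age and gender (or the matched pair) in the model, and all available data used. Name the group-by-time slope difference as the single primary sub-study test, two-sided, and report it with a confidence interval. A repeated measures ANOVA with a group-by-time term, or a comparison of change scores, would also address the aim but handles dropout less well. Keep the visit means as description.

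Restate the sub-study's power for a difference of 7% against 1–2% per year, with the assumed SD of change or within-person correlation, the sidedness, and whether 42 is per group or in total. Say whether the Missing data section covers the sub-study.

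The cost is protocol or analysis-plan wording and slightly more analysis work. No new data, visits or participants are needed for the change of analysis.
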